##### Aim 1: Meeting 24-Hour Movement Guidelines

We will compare the proportion of intervention and control group participants meeting all 3 recommendations at 12 weeks using a chi-square analysis.

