#### Sample Size and Power Calculation

Our analysis is based on a previous home-based routine-based multibehavior intervention in preschool children, which sought to improve similar behaviors, and reported an increase in the proportion of children meeting the screen time guideline increased from 5% to 30% over 12 weeks [23]. Based on our past studies, we estimate that few will meet the screen time guideline [25,62], like the beginning metric of the routine-based study. Given the overlap in content between the routine-based study and this study, we hypothesize that we can also improve the screen time guideline and potentially the remaining behaviors within the same time frame. A minimally important difference in 24-hour movement behaviors is not clear as of October 2025, as there are no other 24-hour movement guideline adherence studies. A sample size of 30 families per arm will provide 80% power to detect a meaningful difference in the proportion of control (1/30, 5%, no change from baseline) and intervention group (10/30, 35%) participants meeting all 3 recommendations at the 12-week visit. Assuming a dropout rate of 25%, we will recruit 40 families per arm (80 total). This power and difference can also be achieved with a minimum of 24 participants per group; while 30 participants per group will have 63.5% power to detect a difference between 5% and 25%, meeting all 3 recommendations; and a 99% power to detect a difference between 5% and 20%, meeting all 3 recommendations. Statistical significance will be set at *P*=.05 for all aim-related analyses.

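### The stated 99% power for 5% versus 20% at 30 per group is impossible; about 45% is the value consistent with the plan's other power figures

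*Protocol article*

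**What the plan says.** The primary comparison, under Aim 1, is of the proportions "meeting all 3 recommendations at 12 weeks using a chi-square analysis". The section on sample size and power adds: "Statistical significance will be set at *P*=.05 for all aim-related analyses". Neither place says whether the chi-square is continuity-corrected or whether the calculation is two-sided.

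That section makes four power statements:

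- For 5% versus 35%: "A sample size of 30 families per arm will provide 80% power to detect a meaningful difference". Allowing for 25% dropout, this becomes 40 recruited per arm.
- For the same contrast: "This power and difference can also be achieved with a minimum of 24 participants per group".
- For a smaller contrast: "30 participants per group will have 63.5% power to detect a difference between 5% and 25"%.
- Continuing that last sentence, with the group size still 30: "a 99% power to detect a difference between 5% and 20%, meeting all 3 recommendations".

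**The concern.** The last two statements cannot both be true. They share the group size, the 5% control rate, the test and the significance level, and only the intervention rate differs. Power rises with the size of the difference, so 15 points cannot be easier to detect than 20. If 63.5% is right for 5% versus 25%, the power for 5% versus 20% must be below 63.5%.

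The issue is how the trial's sensitivity is understood. The article says that no minimally important difference has been established for this outcome, so these sensitivity figures are the reader's only guide to which smaller effects the trial could detect. Smaller effects are plausible. The benchmark study moved the screen time guideline alone from 5% to 30%, whereas this trial's endpoint requires all three guidelines. The earlier 24-hour movement trial described in the Discussion reduced screen time but not the other behaviours. A reader who relied on the 99% could treat a null result as ruling out a 15-point benefit.

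**Working it through.** **Inputs.** From the section on sample size and power: 30 per group (24 for the alternative), control rate 5%, intervention rates 35%, 25% and 20%, significance level 0.05. From Aim 1: a chi-square comparison of two proportions. Allocation is 1:1. Two-sided testing is assumed, because the article does not state it; one-sided results are given below.

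**Formulas.** The arcsine approximation can be followed by hand:

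h = 2·asin(√p₂) − 2·asin(√p₁), power = Φ(h·√(n/2) − 1.960).

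The chi-square and Fisher powers come from exact enumeration: the probabilities of all pairs of outcomes from two Binomial(n, p) arms for which the test gives P ≤ 0.05 are added up.

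**Step 1: reproduce the article's own figures.**

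- 5% versus 25%, n = 30: h = 1.0472 − 0.4510 = 0.5962; 0.5962 × √15 = 2.309; Φ(2.309 − 1.960) = Φ(0.349) = 63.6%. Exact uncorrected chi-square gives 63.3%. The article says 63.5%.
- 5% versus 35%, n = 24: h = 1.2661 − 0.4510 = 0.8151; 0.8151 × √12 = 2.824; Φ(0.864) = 80.6%. Exact uncorrected chi-square gives 80.8%. The article says 80%.

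Both methods therefore match the article's figures closely.

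**Step 2: apply the same methods to 5% versus 20%, n = 30.**

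h = 0.9273 − 0.4510 = 0.4763; 0.4763 × √15 = 1.845; Φ(1.845 − 1.960) = Φ(−0.115) = 45.4%. Exact uncorrected chi-square gives 45.3%.

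**Step 3: all scenarios at 30 per group, two-sided 0.05.**

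| Contrast | Article | Arcsine | Uncorrected chi-square | Fisher |
|---|---|---|---|---|
| 5% vs 35% | 80% | 88.4% | 88.0% | 78.8% |
| 5% vs 25% | 63.5% | 63.6% | 63.3% | 43.6% |
| 5% vs 20% | 99% | 45.4% | 45.3% | 24.1% |
| 5% vs 50% | not given | 99.1% | 99.2% | 98.2% |

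**Step 4: look for any variant that gives 99% for 5% versus 20%.**

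- Other two-sided methods at n = 30: 41.7% (pooled normal), 43.8% (unpooled), 27.1% (continuity-corrected normal), 24.1% (Yates).
- One-sided at n = 30: the highest value is 57.9% (arcsine). The one-sided normal and arcsine methods without continuity correction give 71% to 75% for 5% versus 25%, so they do not match the stated 63.5%.
- Two-sided with all 40 per arm retained: at most about 57%.
- Group size needed for 99% power, by the pooled normal formula: [1.960·√(2 × 0.125 × 0.875) + 2.326·√(0.0475 + 0.16)]² / 0.15² = (0.9167 + 1.0597)² / 0.0225 = 173.6, that is 174 per arm.

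No variant comes near 99%.

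**The case against.** The strongest reply is that the figure drives nothing. The sample size rests on 5% versus 35% at 30 evaluable per arm, where power is 88% by uncorrected chi-square and about 79% by Fisher, and 30/0.75 = 40 is correct. The 99% is a closing sensitivity remark that enters no analysis or decision rule. It may also be a misprint: 5% versus 50% at 30 per group gives about 99%. An attentive reader would see the conflict with the 63.5% at once. All of this limits the consequence, but none of it makes the printed statement true. The article does not confirm a misprint, so the intended scenario cannot be recovered from it.

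A second reply is that 45% depends on an uncorrected test, which the article does not specify. That is fair. The expected number of successes per arm is 30 × 0.125 = 3.75 for 5% versus 20% and 30 × 0.15 = 4.5 for 5% versus 25%. Both are below the usual threshold of 5, where Fisher's test is often substituted. On that basis the powers would be about 24% and 44%, which is further from 99%.

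Three stronger readings are tempting and are not supported:

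- A reader might infer that the paragraph mixes methods, because both 24 and 30 per group are credited with 80% power for 5% versus 35%. If 80% is read as at least 80%, one method fits both: uncorrected chi-square gives 80.8% at 24 and 88.0% at 30.
- A reader might make something of the bracketed counts in "control (1/30, 5%, no change from baseline) and intervention group (10/30, 35"%, since 1/30 is 3.3% and 10/30 is 33.3%. But 5% and 35% of 30 are 1.5 and 10.5, cut to whole children. This is trivial rounding on which nothing depends.
- A reader might infer that the conclusion of a negative trial would be wrong. That does not follow, because a null result is judged mainly on the estimate and its confidence interval.

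**Conclusion.** The 99% figure is wrong as written, and its own sentence shows this without any calculation. Under the two-sided methods that reproduce the article's other figures, power at 30 per group for 5% versus 20% is about 45%; with Fisher's test it is about 24%. The chance of missing a 15-point effect is thus about 55% or more, and a null result could not be taken to exclude such an effect.

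That more-likely-than-not statement assumes 30 evaluable per group and two-sided testing. It would not hold for one-sided normal or arcsine calculations without continuity correction (54.6% to 57.9% power), or for uncorrected two-sided tests if all 40 per arm were retained (53% to 57%). The impossibility of 99% depends on neither assumption.

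A reader might go on to infer that the trial is too small for its stated aim. The documents do not support this: the contrast on which the trial was sized, with 30 evaluable and 40 recruited per arm, is unaffected. The error lies in the reported sensitivity to smaller effects.

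**What to change.** Replace 99% with about 45% for 5% versus 20%. If a different scenario was intended, correct the scenario instead; 99% at 30 per group corresponds to roughly 5% versus 50%. Only the authors can say which was meant.

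State the test variant and sidedness behind the calculation, and give every power on that one basis. For an uncorrected two-sided chi-square at 30 per arm, the set is 88% for 5% versus 35%, 63% for 5% versus 25% and 45% for 5% versus 20%, with 81% at 24 per arm for 5% versus 35%. If Fisher's test is the planned analysis, the 30-per-arm values are about 79%, 44% and 24%, and 24 per arm gives about 71% for 5% versus 35%, so the statement about a minimum of 24 would also need revising.

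The work is a correction to one paragraph, and to any other document that repeats the figure. Results are expected in 2027, so it can be made before they are interpreted. Enrolment does not change, and the only cost is a less favourable stated power for small effects.

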#### Exploratory Aims

We will also conduct an intent-to-treat analysis using a log-binomial regression or Poisson with robust variance to adjust for baseline recommendation number and randomization strata (age and sex). Linear regression will also be used to compare changes in exploratory outcomes between treatment and control groups with adjustment for baseline values. If demographic differences, such as income, are found between the 2 groups, we will conduct a sensitivity analysis with these variables for adjustment. These exploratory outcomes include, in priority order: number of recommendations obtained (range: 0-3), individual 24-hour movement behaviors, anthropometry, early child motor battery scores, early child cognitive battery scores, executive functioning scores, and behavioral problem scores. Descriptive characteristics will also be explored, such as PA and accessibility score, household chaos score, parental support of PA, parental perceived influence on screen time, family regularity index, child preferences for PA, and theoretical component changes (eg, intention and behavioral support for PA). We will also explore the ideal change in behaviors using isotemporal substitution analysis, whereby evaluating substitution of one behavior (eg, sedentary behavior) for another (eg, MVPA) with change in child developmental outcomes.

Furthermore, we will examine the relationship between meeting specific recommendations and child outcomes, with a mediator of theoretical component changes (eg, habit formation scores). Mediation analysis will be conducted using the PROCESS vs 3.5 macro with 10,000 bootstrap intervals with unstandardized estimates and CIs [63]. These exploratory outcome testing will be subject to the Benjamini-Hochberg adjustment for multiple comparisons [64].

As for missing data, we will describe differences in baseline characteristics between participants with complete versus incomplete follow-up. Sensitivity analyses based on multiple imputation methods will be conducted to examine the robustness of our findings with respect to missing data.

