#### Follow-up Visits (Week 6 and Week 12)

At the second visit (approximately 60-90 min; week 6), families return to complete preschooler anthropometrics, preschooler development tests, and parent questionnaires. Procedures are completed similarly to the baseline visit. Preschoolers are fitted with an accelerometer, and parents are asked to return the device, activity or sleep log, and home inventory after 2 weeks of wear. The trained staff answer any questions on the mobile app for families in the intervention group.

At the final visit (approximately 60-90 min; week 12), families return to complete preschooler anthropometrics, preschooler development tests, and parent questionnaires. Procedures are completed similarly to the baseline visit. Preschoolers are fitted with an accelerometer, and parents are asked to return the device, activity or sleep log, and home inventory after 2 weeks of wear. Parents in the intervention are allowed to delete the mobile app or continue viewing the content. Parents randomized to the control are allowed to download the mobile app, receive a tutorial, and access all mobile app lessons and features.

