#### Exploratory Outcomes

##### Parent Report of 24-Hour Guideline Adherence

Parents will report how many days per week (range: 0-7) their child obtains at least 180 min/d of total PA and at least 60 min/d of MVPA. Staff members describe total PA as including any activity, such as slow or easy movement, based on direct report observations of preschooler’s movement [42]. These may include walking, light dancing, playing catch, and easy bike riding. MVPA includes any “huff and puff” activity that increases their heart rate, such as playing a sport, more intense dancing, and running. If parents have trouble discerning days, the staff will ask them about the past week. Furthermore, parents will be asked on average how much overnight sleep and time their child spends napping, in separate questions with free response options, which are summed for a total amount of sleep during the day. The sleep questions have demonstrated moderate correlations with accelerometry measures [43]. Parents are also asked about screen time (refer to “Primary Outcomes” section). We chose these questions based on national surveys of child PA [44] and surveillance efforts of child movement behaviors [40,45]. This information is gathered during the phone screening process, where trained staff members ensure parents consider both weekdays and weekends, and any changes due to nontypical weeks, to obtain accurate habitual behavior amounts. Screening questions related to total PA, MVPA, and sleep are repeated at week 6 and week 12.

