#### Recruitment Plans

We will use various existing modalities of recruitment in the selected area to ensure the recruitment amount is achieved. As part of this 12-week study, participants are contacted every 2 weeks or up to 1 month to schedule visits and pick up accelerometers. All available data will be sought in the case of discontinuation after visit 1, with the priority of 24-hour movement behavior data (questionnaire and accelerometry), other questionnaires, then anthropometry, cognition and motor skill assessments.

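### The week 6 outcome data have no stated role in any between-arm comparison; a repeated-measures model would use them and protect against loss that depends on week 6 response

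*Protocol article*

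**What the plan says.** Follow-up Visits (Week 6 and Week 12) describes a full mid-trial assessment: "At the second visit (approximately 60-90 min; week 6), families return to complete preschooler anthropometrics, preschooler development tests, and parent questionnaires". A second wear period starts there, after which "parents are asked to return the device, activity or sleep log, and home inventory after 2 weeks of wear". The section on parent-reported adherence adds: "Screening questions related to total PA, MVPA, and sleep are repeated at week 6 and week 12". Almost everything measured at week 12 is therefore also measured at week 6.

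The stated analyses are narrower:

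- **Aim 1:** "We will compare the proportion of intervention and control group participants meeting all 3 recommendations at 12 weeks using a chi-square analysis".
- **Exploratory Aims, adherence:** a log-binomial or robust Poisson regression adjusts for the baseline number of guidelines met and the randomization strata. Week 6 is not mentioned.
- **Exploratory Aims, other outcomes:** "Linear regression will also be used to compare changes in exploratory outcomes between treatment and control groups with adjustment for baseline values". The visit at which change ends is not given, and no repeated-measures model is named.
- **Missing data:** baseline characteristics of families with complete and incomplete follow-up are compared, and "Sensitivity analyses based on multiple imputation methods will be conducted to examine the robustness of our findings with respect to missing data". Recruitment Plans adds: "All available data will be sought in the case of discontinuation after visit 1".

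The sample size section allows for 25% loss. Results reports 39 families randomized, 28 final visits completed and one loss as of October 2025.

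**The concern.** A regression of change uses one follow-up value per child. If that value is week 12, a child without a week 12 result drops out of the comparison, although the week 6 result is likely to be the best available predictor of the missing one. This can happen in two ways: the family leaves after week 6, or it stays but the week 12 recording fails the wear rule under Primary Outcome (at least 3 days of 10 hours, including a weekday and a weekend day, plus 3 days of sleep). For movement outcomes, missingness can therefore exceed visit dropout.

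If intervention families who see little change by week 6 are the ones who go missing, the remaining intervention children look better than the randomized group and the effect is overstated. Such a pattern is plausible in this design. The Figure 3 caption says controls receive the app only after completing all week 12 measures, which gives them a reason to stay that intervention families lack. The documents do not show that it occurs.

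The planned comparison of baseline characteristics would reveal loss driven by week 6 response only indirectly.

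**Working it through.** **Inputs from the protocol article.** 40 per arm; 25% planned loss; 1 of 39 lost so far (1/39 = 2.6%); outcome visits at weeks 6 and 12. The plan's inflation reproduces: 30 / (1 − 0.25) = 40 per arm. Families without a final visit and not counted as lost: 39 − 28 − 1 = 10, if the one loss is not among the 28.

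**Assumed inputs (not in the documents).** True effect 0.50 SD at week 12; all missingness arises after week 6; the chance of loss follows a logistic function of the week 6 value; correlations as listed. Sets A and C also assume an effect of 0.25 SD at week 6.

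**Estimators.** (1) Regression of baseline-to-week-12 change on arm and baseline, in children with week 12 data. (2) A likelihood estimate that uses week 6: regress week 6 on arm and baseline in all children (arm coefficient a); regress week 12 on arm, baseline and week 6 in observed children (arm coefficient c, week 6 coefficient b); the estimate is c + b × a.

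**Results (mean estimate; truth 0.50).**

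| Set | Loss | Change regression | Using week 6 |
|---|---|---|---|
| A: all correlations 0.5 or 0.7, 3,000 trials per setting | 25%, random | 0.50 | 0.50 |
| A | 25%, week 6-dependent, both arms | 0.49 to 0.50 | 0.50 to 0.51 |
| A | 25%, week 6-dependent, intervention arm only | 0.54 to 0.55 | 0.50 |
| A | 2.6%, any mechanism | 0.50 to 0.51 | 0.50 to 0.51 |
| B: 0.5 with baseline, 0.7 between weeks 6 and 12, 6,000 trials | about 27%, intervention arm only | 0.582 | 0.507 |
| B | random | 0.500 | 0.500 |

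Set A gives a bias of +0.043 to +0.053 SD (0.043/0.50 = 9%; 0.053/0.50 = 11%). Set B gives +0.082 SD (16%).

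Set C used B's correlations and varied how steeply intervention-arm loss depends on week 6 (log-odds slope 0.5 to 1 per SD). The change regression averaged 0.55 to 0.60 at 25% missing, 0.53 to 0.56 at 15%, 0.52 to 0.54 at 10% and about 0.51 at 2.5%. The week 6 estimate stayed at 0.50.

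**Why the sets differ.** The bias is roughly the week 6 coefficient b times the shift in mean week 6 value (given baseline) among retained intervention children. On the SD scale, b = (r6,12 − r0,6 × r0,12) / (1 − r0,6²).

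- All correlations 0.5: (0.5 − 0.25) / 0.75 = 0.33.
- All 0.7: (0.7 − 0.49) / 0.51 = 0.41.
- 0.5, 0.5 and 0.7: (0.7 − 0.25) / 0.75 = 0.60.

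Set A at 0.5 implies a shift of 0.053 / 0.33 = 0.16 SD. The same shift with b = 0.60 gives 0.60 × 0.16 = 0.10 SD, the top of set C. The more week 6 says about week 12, the larger the bias from leaving it out.

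**Precision under random loss.** Set A: empirical standard error 0.228 against 0.224, and 0.185 against 0.182, so about 3% less variance. Set B: 0.226 against 0.220, about 3% in standard error.

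**The case against.** The strongest reply has four parts.

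**The wording leaves room.** A reader might infer that the plan fixes a two-point analysis and throws week 6 away. The text does not say so: it leaves the end of the change open and excludes no data. Separate regressions at weeks 6 and 12 would fit it. This stands, although such regressions would still leave a child missing at week 12 out of the week 12 contrast.

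**Missing data are addressed.** Multiple imputation is planned and can use week 6 values, so it is wrong to say that such a family can contribute nothing. Imputation variables and visit definitions are also details that an article often leaves to a full analysis plan, which is not shown. That too stands. What remains is that imputation is only a sensitivity analysis, while the method named for the main comparison takes one follow-up value per child.

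**The bias needs a particular pattern.** A reader might infer that the estimates are generally open to dropout bias. They are not. It takes substantial loss that depends on week 6 response differently by arm, and nothing in the documents shows this. Even 0.08 SD is about a third of the estimate's own sampling SD (0.082/0.228 = 0.36). Loss so far is low, though about 10 families were still in follow-up and the allowance is 25%.

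**Scope is small.** Baseline-adjusted regression is a valid randomized comparison, and these outcomes are exploratory and subject to Benjamini-Hochberg adjustment. Week 6 data cannot help with families lost before week 6. All of this is correct, and it makes the point an improvement, not a repair of an error.

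**Conclusion.** The point holds as a low-cost improvement. The article collects a full set of week 6 outcomes and gives them no stated part in any between-arm analysis. If change is measured to week 12, the main exploratory regressions omit children seen at week 6 but missing later.

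The size is conditional on the assumed inputs above. It is about 0.04 to 0.08 SD on a 0.50 SD effect when about 25% are lost and loss follows week 6 response in the intervention arm only, reaching 0.10 SD in the steepest setting tried. It is about 0.01 SD or less when loss is random, works alike in both arms, or stays near 2.6%. Using week 6 removed nearly all of the bias, and in none of these runs was it less precise. This presumes that loss depends on observed data; no method based on week 6 corrects loss driven by unobserved week 12 values.

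The documents do not support reading this as a flaw in the primary result: the Aim 1 test, the sample size and the power are untouched.

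**What to change.** 1. In Exploratory Aims, state the visit at which change ends.
2. For continuous exploratory outcomes, replace the regression of change with a mixed model for repeated measures: weeks 6 and 12 as outcomes; arm, visit and arm by visit; baseline value, age and sex as covariates. Report the week 12 arm contrast.
3. Name week 6 guideline status and movement behaviors as variables in the multiple-imputation model for adherence to all 3 guidelines.

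**Cost.** No new data, and slightly more analysis work. A covariance structure must be specified; with two follow-up visits an unstructured one has three parameters (two variances and one covariance). The number of guidelines met (0 to 3) is a short count and may need an ordinal or count version of the model. Results are expected in 2027, so the change can be made before analysis.
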